### *Secondary outcomes*

#### Time to PPI discontinuation

- Survival analysis of PPI discontinuation, considered the time until complete withdrawal since recruitment (Kaplan-Meier method);

#### Change in other Medication-related parameters | Profile and Safety outcomes.

- Medication burden that is, the mean number of regular medications patient take and proportion of patients on polypharmacy (patients with 5 or more medicines as commonly accepted definition (89)), assessed at baseline and 6-month follow-up.
- Drug-drug interactions (DDIs), that is, the absolute and relative counts of drug-drug interactions and by degree of severity, patients with any drug-drug interaction and with severe interactions. Most frequent severe drug-drug combinations will also be reported. Drug-drug interactions will be assessed by sifarma® software interaction alert system considering all medications taken, assessed at baseline and 6-month follow-up. Moderate and serious DDIs will be checked by the researchers using the Sifarma® software safety module. This module is an Electronic Information platform on medicines integrated on the Sifarma® dispense software, with updated information regarding clinically relevant Drug-Drug interactions (DDIs). This platform is powered with the summary of medicine characteristics (RCM) and other information sources as Stokley's Drug Interactions and Lexicomp. DDIs are classified according with 2 types of severity: a) Moderate DDI - Drug associations which benefit from (or for which it is recommended) monitoring, dose adjustment or any other form of management; b) Severe DDI - potential life-threatening and/or requiring medical intervention to minimize or prevent serious adverse effects; drugs are contraindicated for concurrent use. The software

displays an automatic alert regarding the DDIs identified and provide additional information regarding the mechanism of interaction.

- Adverse drug events, that is, the absolute and relative counts of self-reported adverse drug events and type of events (e.g., needed professional support) experienced by patients, assessed at baseline and 6-month follow-up.

#### Change in Patient Reported Outcomes Measures (PROMs):

- Quality of life related to health, will be evaluated using the five-level version of the European Quality of Life-5 Dimensions questionnaire (EQ-5D-5L instrument) (90,91), assessed at baseline and 6-month follow-up; EQ-5D-5L scores will be computed for each patient.
- Patients' beliefs about inappropriate medicines, assessed by the beliefs about medicines questionnaire (BMQ-specific)(92) applied to PPI; assessed at baseline and 3-month follow-up. It comprises two sub-scales: the specific necessity scale (SNS) assessing patients' views on their personal need for their medication and the specific concerns scale (SCS) assessing patients concerns towards their medication.
- Adherence using a self-reported 7-item Measure Treatment Adherence (MTA) tool (93), applied at baseline and 6-month follow-up. The MTA, a psychometric tool derived from Morisky et al, evaluates the individuals' behaviour in relation to the daily use of medication. Each item is scored from 1 (always) to 6 (never). Points are summed and divided by the total number of items. Higher scores indicate higher self-reported adherence. Patients with values of 5 and 6 are considered adherents. We select this method to measure multiple medication adherence because is simple to apply and was validated for the Portuguese Population in 2001, with a reported Cronbach's alpha of 0.74.

#### Patient reported experiences measures (PREMs)

- Satisfaction with the collaborative intervention (general and health professional related), measured by a 5-point Likert scale at 6-month follow-up in the intervention group.

Process outcomes, will be measured only in the intervention arm and will be used to assess the fidelity and quality of the collaborative intervention:

- Proportion of GP replies to the initial report of the pharmacy;

- Number and type of pharmaceutical opinions sent by the pharmacist to the GP;
- Number and type of GP decisions related to PPI deprescribing and safety data;
- Proportion of concordant pharmacist opinion-GP deprescribing decision;
- Proportion of patients who experienced the follow-up telephone contact by the pharmacist accordingly to the intervention protocol and;
- Health professional's compliance with predefined intervention steps times.

Table 4 illustrates a summary of time points and parameters measurements in both trial arms and process measurements collected only in the intervention arm for fidelity and quality analysis.

**Table 4 - Overview of data collection schedule and measurements**

| Time points / Data                                    | T0              | Ongoing (only intervention arm) | T1       | T2       |
|-------------------------------------------------------|-----------------|---------------------------------|----------|----------|
|                                                       | Recruitment - 0 | Intervention time span          | 3 months | 6 months |
| Socio-demographic and clinic characterization         | X               |                                 |          |          |
| Self-rated health status (SRH)(94)                    | X               |                                 |          |          |
| PPI specific outcomes                                 | X               |                                 | X        | X        |
| Other medication related outcomes                     | X               |                                 |          | X        |
| Quality of life (EQ-5D-5L)(90,91)                     | X               |                                 |          | X        |
| BMQ specific(92) applied to PPI                       | X               |                                 | X        |          |
| Adherence (MTA)                                       | X               |                                 |          | X        |
| Healthcare resource utilization (Economic Evaluation) | X               |                                 |          | X        |
| Intervention satisfaction questionnaire               |                 |                                 |          | X        |
| Process parameters                                    |                 | X                               |          |          |

## 6.9. Blinding

Due to the nature of the intervention, neither patients nor pharmacist and GPs (providers) are blinded to the intervention. In addition, research team who developed this trial cannot be blinded either. However, to preserve a certain level of masking, to protect sources of bias, intervention participants will only be aware that the research team will also collect data in other geographical regions regarding usual care.

In the control group, no information regarding the intervention procedures will be provided to pharmacies and patients. The project will be presented as a medication use pattern study in the elderly. Moreover, as pharmacies allocated to each group (intervention and control) are located in distinct geographic locations, minimizing their interactions and ensuring their unawareness of each other.

FHUs in the control sites will be blind by design as they do not have any intervention in this trial, serving only to ensure that patients in both arms are subject to the same type of usual care.

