### **6.8. Outcomes**

The outcomes are measured at patient level. Patient's outcomes data will be collected at baseline and at study follow-up points (3 and 6 months). Follow-up data can be collected within 1 month after or before these exact time-point. At baseline, data collection is performed through a face-to-face interview conducted by the pharmacist (before the intervention take place in the intervention arm), by electronic extraction from the pharmacies dispense software and by telephone interview led by the research team after the patient recruitment. Follow-up study data collection is conducted by the research team through patients' telephone interview and electronic extractions from the pharmacies dispense software. Intervention related data will be collected alongside the study.

For process outcomes and economic evaluation analysis, data will be collected from the intervention log form (**Annex 10**), from the case report form "Passaporte do utente" (**Annex 9**) developed for the information exchange between pharmacists and GP, and from the CRA monitoring form (**Annex12**). These materials will be collected for study purposes in the end of the intervention period.

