#### **6.11. Sample size**

Our principal hypothesis is that our intervention will reduce the use of inappropriate PPIs compared to usual care.

Our assumption is that the intervention will reach a rate of discontinuation similar with that achieved in previous studies reporting medication withdrawals in intervention with collaborative work between pharmacists and GP, compared to usual care (minimum absolute difference of 20%)(79,97). Alongside,

we will also assume that a small rate of discontinuation will be observed in the group without the intervention (control Group) as much as of 10%.

Therefore, our study will be conducted to detect a minimal 20% increase in the rate of discontinuation of inappropriate medication use caused by the intervention compared with the usual care. Assuming an alpha of 5%, 90% power and an allocation ratio of 1:1, we estimate that the minimum total sample size to detect differences between intervention and control group is 178 patients (89 patients per group).

Considering a 20% lost to follow-up, then a total of 222 patients (111 per group) recruited in the participating pharmacies will be needed in this study.

The sample size was calculated using the software G\*Power version 3.1.9.6.

**Exact** - Proportions: Inequality, two independent groups (Fisher's exact test)

**Options:** Exact distribution

**Analysis:** A priori: Compute required sample size

|                |                             |   |           |
|----------------|-----------------------------|---|-----------|
| Input:  | Tail(s)                     | = | Two       |
|                | Proportion p1               | = | 0.1       |
|                | Proportion p2               | = | 0.3       |
|                | $\alpha$ err prob           | = | 0.05      |
|                | Power (1- $\beta$ err prob) | = | 0.90      |
|                | Allocation ratio N2/N1      | = | 1         |
| Output: | Sample size group 1         | = | 89        |
|                | Sample size group 2         | = | 89        |
|                | Total sample size           | = | 178       |
|                | Actual power                | = | 0.9017447 |
|                | Actual $\alpha$             | = | 0.0340267 |

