### **9.4. Declaration of interests**

This research is conducted by CEFAR/Infosaúde, the research center of the ANF, which has vested interests in this topic and funded the research.

Neither the pharmacists, nor the general practitioners or subjects enrolled in the study will be remunerated for their participation in the study. Additionally, the support by academic independent researchers, who do not receive any fees for collaboration, will guarantee that these interests do not interfere in the analysis and interpretations.

These conflicts of interests will obviously be declared in all scientific publications.

The research team guarantees that outcomes of the project will be submitted for publication, regardless of the positive, negative, or non-significant impact of the intervention.

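### An unmasked research team elicits by telephone the PPI report that helps decide the primary outcome; this detection bias can be partly reduced, and section 7 does not list it

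*Protocol*

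**What the plan says.** Protocol section 6.9 states that patients, pharmacists and GPs know the arm, and adds: "In addition, research team who developed this trial cannot be blinded either". The masking measures it does describe concern what participants and control sites are told. None concerns the person who collects the outcome.

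On follow-up, section 6.8 says: "Follow-up study data collection is conducted by the research team through" telephone interviews and extractions from the dispensing software. Section 6.5 gives the research team the baseline, 3-month and 6-month calls in both arms.

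Section 6.8 describes the primary outcome as ascertained from sales linked to the tax number and confirmed by self-report. Its two operational criteria are then a lack of reported consumption or a reported dose reduction, each without a new drug of the same class. Section 6.15.4 limits the primary analysis to patients with a 6-month report of PPI use.

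Section 9.4 describes the organisation that conducts the study as one "which has vested interests in this topic and funded the research".

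**The concern.** The caller knows the arm and works within the team that wrote the intervention booklet, trains the pharmacists and draws up the therapeutic profile passed to the GP. Whether a patient has stopped, reduced or is still taking a PPI at the same dose can depend on how far the caller probes and how a vague answer is coded. If that differs by arm, it enters the primary risk difference, the relative risk and the number needed to treat directly.

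The stated safeguard against the organisation's interest, unpaid independent academics, covers analysis and interpretation (sections 6.13 and 9.4). It does not cover how the outcome is elicited. Section 7 lists self-report and recall under information bias and presents the research-team interview as a means of validation. It does not mention the interviewer's knowledge of the arm.

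**Working it through.** **1. Does the call decide the outcome?**
- Section 6.8: sales and self-report are both sources, but both operational criteria are worded as reports.
- Section 6.15.4: without a 6-month report the patient is not in the primary analysis.
- Table 5: continuous PPI use at 3 and 6 months comes from pharmacy software confirmed by telephone. The discontinuation date comes from the telephone interview alone.
- The protocol does not say which source prevails if sales and report disagree.

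The call therefore matters, alongside a second source that does not depend on the caller.

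**2. What in the call reveals the arm?**
- At 3 months, Table 4 lists PPI outcomes and the beliefs questionnaire, the same in both arms.
- At 6 months, Table 5 adds two kinds of telephone item for the intervention arm only: satisfaction, and GP appointments related to the intervention.
- Health unit name is a consent-form field. The pharmacy code is held at all three time points. Either one identifies the arm. The study ID (initials and date of birth, section 6.13) does not.

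**3. The plan's own figure.** Section 6.11 works from "Assuming an alpha of 5%, 90% power and an allocation ratio of 1:1", a control rate described as "a small rate of discontinuation will be observed in the group without the intervention (control Group) as much as of 10" per cent, a "minimum absolute difference of 20" per cent, and the option "Proportions: Inequality, two independent groups (Fisher's exact test", two-tailed. The exact power of Fisher's test, summed over two independent binomials at 10% and 30%, is 0.8977 with 88 per group and 0.9017447 with 89. The stated minimum, which "is 178 patients (89 patients per group", is reproduced, and so is its stated power. Masking the call does not change this number.

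**4. Illustration only.** The documents give no misrecording rate. Let f be the share of true non-successes in the intervention arm recorded as successes, with no error in the control arm and no correction from sales.

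Under the planning rates, the apparent difference is (0.30 + 0.70f) − 0.10:

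| f | Apparent difference | NNT |
|---|---|---|
| 0 | 20.0 points | 5.0 |
| 2% | 21.4 points | 4.7 |
| 5% | 23.5 points | 4.3 |
| 10% | 27.0 points | 3.7 |

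With no true effect (10% in both arms), the recorded intervention rate is 0.10 + 0.90f. The chance that Fisher's test with 89 per group rejects is:

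| f | Spurious difference | Rejection rate |
|---|---|---|
| 0 | 0 points | 3.0% |
| 2% | 1.8 points | 4.3% |
| 5% | 4.5 points | 10.7% |
| 10% | 9.0 points | 32.9% |

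Fisher's test is used because it underlies the sample size. The planned analysis is an adjusted binomial model.

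The direction is also an assumption. If a cautious caller instead missed 5% or 10% of true successes in the intervention arm, the difference would fall to 0.30 × 0.95 − 0.10 = 18.5 points or 0.30 × 0.90 − 0.10 = 17.0 points.

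**The case against.** The strongest reply is that the outcome is not purely self-reported. Sales linked to the tax number are a named source in sections 6.8 and 6.17.4 and in Table 5. Section 6.11 reports that about 94% of PPI sales prescribed in the two intervention health units took place in the selected pharmacies, with under 1% of PPI dispensing there without prescription. That is a real check on the caller, and it stands. It is incomplete: actual coverage depends on which pharmacies join, no control-arm figure is given, and the report still governs the criteria and entry to the analysis.

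A reader might infer that masked calls are available with existing staff at no extra cost. The documents do not support this. They give no number of callers and identify no member unaware of the arm, and the team itself makes the baseline calls and drafts the profiles.

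A reader might also infer that the bias is fully avoidable. It is not. Intervention patients have had a booklet, a GP contact and at least one pharmacist call, and may mention them as soon as PPI use is raised. Their own tendency to report success is not changed by masking the caller.

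Finally, the 6-month questionnaire is not shown and may already ask about PPI use first. The protocol text does not fix the order.

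**Conclusion.** The concern holds as a risk of detection bias that can be partly reduced and that the protocol neither mitigates nor acknowledges. The reason given in section 6.9 applies to those who developed the trial. It does not explain why every follow-up caller must know the arm.

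It would go too far to read the illustrative inflation of 3.5 to 7.0 points (0.70 × 5% and 0.70 × 10%) as an estimate, or to say that the result is biased toward the intervention. Those figures rest on an assumed error rate, confined to one arm and one direction, with no correction from sales. They show only that modest differential recording would matter against a planned 20-point difference. The change is worth making because it is cheap and bears on the primary outcome. The sample size is not affected.

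**What to change.** - **Call sheet, 3 and 6 months:** give callers study ID, telephone number and the PPI dispensing details to be confirmed, without arm, health unit name or pharmacy code. Where staffing allows, which the sponsor must confirm, use team members who did not handle that patient's baseline call or therapeutic profile.
- **6-month interview (Annex 14):** record and lock PPI use and dose before the satisfaction and intervention-related GP items open. The items listed for 3 months need no reordering.
- **Classification:** derive the primary outcome from sales and report by a programmed rule, with the arm code withheld. The rule should say what happens when the two sources disagree.
- **Section 6.9:** limit the statement on blinding to the roles it applies to, and describe these steps.
- **Section 7:** list the remaining interviewer and patient reporting bias.

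The cost is minor script and database work. The note to Table 6 already allows minor script adjustments. The data are already being collected, and the ordering, locking and programmed classification do not depend on an additional assessor. The limit is that masking stays partial, since patients may disclose their arm. Recording at each call whether that happened would show how far the masking held.

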#### **6.10. Potential harms and patient safety**

Because of the pharmacological characteristics of the PPI there is a possibility that the discontinuation might lead to symptoms relapse (e.g., rebound hyperacidity) or complications (95). However, the potential for serious harm due to adverse drug withdrawal events (ADWEs) appears to be rare (96) and several drug class specific deprescribing interventions have found no difference in the rate of ADWEs between control and intervention groups (35). We expect a low probability of relapses or complications as only non-evidenced based medications will be withdrawn and the best evidence deprescribing guidelines will be followed (87). Additionally, patients will have the pharmacist and general practitioner support to help them to manage potential symptomatology with non-drug approaches, use of OTC medicines or, if necessary, to review the PPI dose, indication to use on-demand or full restart of the medication based on the best evidence. Any suspected adverse drug event (ADE) acknowledged will be reported to the study research team and to the National Pharmacovigilance System through "Portal RAM" from the National Authority of Medicines and Health Products, I.P (INFARMED) site.

#### **6.11. Sample size**

Our principal hypothesis is that our intervention will reduce the use of inappropriate PPIs compared to usual care.

Our assumption is that the intervention will reach a rate of discontinuation similar with that achieved in previous studies reporting medication withdrawals in intervention with collaborative work between pharmacists and GP, compared to usual care (minimum absolute difference of 20%)(79,97). Alongside,

we will also assume that a small rate of discontinuation will be observed in the group without the intervention (control Group) as much as of 10%.

Therefore, our study will be conducted to detect a minimal 20% increase in the rate of discontinuation of inappropriate medication use caused by the intervention compared with the usual care. Assuming an alpha of 5%, 90% power and an allocation ratio of 1:1, we estimate that the minimum total sample size to detect differences between intervention and control group is 178 patients (89 patients per group).

Considering a 20% lost to follow-up, then a total of 222 patients (111 per group) recruited in the participating pharmacies will be needed in this study.

The sample size was calculated using the software G\*Power version 3.1.9.6.

**Exact** - Proportions: Inequality, two independent groups (Fisher's exact test)

**Options:** Exact distribution

**Analysis:** A priori: Compute required sample size

|                |                             |   |           |
|----------------|-----------------------------|---|-----------|
| Input:  | Tail(s)                     | = | Two       |
|                | Proportion p1               | = | 0.1       |
|                | Proportion p2               | = | 0.3       |
|                | $\alpha$ err prob           | = | 0.05      |
|                | Power (1- $\beta$ err prob) | = | 0.90      |
|                | Allocation ratio N2/N1      | = | 1         |
| Output: | Sample size group 1         | = | 89        |
|                | Sample size group 2         | = | 89        |
|                | Total sample size           | = | 178       |
|                | Actual power                | = | 0.9017447 |
|                | Actual $\alpha$             | = | 0.0340267 |

Monthly sales data retrieved from the pharmacies' system (hmR database®) shows that in 2021 and YTD:May22, the number of packages sold every month per pharmacy of PPI is about 340 in this municipalities and is rising. This number is 16.2 % lower in Arcos de Valdevez (320) than in Ponte da Barca (380).

[figure not shown]

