## 5. Study Design

This is a pragmatic, multicentre, non-randomised controlled trial with a follow-up period of 6 months of a collaborative Pharmacy-Family Health Unit deprescribing intervention. There are two-arms in this controlled trial: the intervention arm (collaborative intervention) and the control arm (usual care). Pragmatic trials are undertaken in the real world under the context of a real-life setting and the results are intended to support a decision to deliver the intervention in a routine practice (85).

An experimental design with random assignment was not feasible since the collaborative intervention was developed based on the expressed interest of two specific family health units (FHUs) – FHU Terra da Nóbrega in Ponte da Barca municipality and FHU Uarcos municipality in Arcos de Valdevez (both belonging to Aces Alto Minho, Unidade Local de Saúde do Alto Minho). Randomization at patient level was not considered to prevent individual contamination, due to controls and interventions being exposed to the same environment (pharmacies and FHUs). Each FHU unit and surrounding pharmacies will consist of a study site (intervention or control).

The Ponte da Barca and Arcos de Valdevez sites will comprise the intervention arm. Control sites will be selected from other geographical regions with characteristics like the intervention study sites.

Patients will be recruited through community pharmacies. A 1:1 ratio (intervention:control) of participants will be used. The flowchart of the C-SENIoR trial is illustrated in Figure 1.

An Economic evaluation will be conducted alongside the trial, meaning the collection of costs and outcome data alongside the trial.

[figure not shown]

Figure 1 - Study Flowchart

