#### **Primary outcomes**

Primary outcome of the study will be calculated using a GLM model for binary outcome with an identity link function to estimate the risk difference or the difference between Intervention and Control groups in the proportion of patients who discontinued or decreased PPI dosage at 6 months of follow up. Results will be adjusted for baseline covariates. Relative risk will be computed as well as the number needed to treat (NNT) – the inverse of the difference in absolute rate of discontinuation between the intervention and control groups. Analysis will also be conducted at 3 months of follow up. A 1 year analysis can be conducted to measure the maintenance of the intervention effect. Significance level adopted is  $\alpha = 0.05$ .

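### The 90% power rests on independent patients although whole sites are allocated, and the primary GLM as written makes no provision for clustering

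*Protocol*

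**What the plan says.** **Allocation (Protocol, section 5).** "Each FHU unit and surrounding pharmacies will consist of a study site (intervention or control"). Two sites, Ponte da Barca and Arcos de Valdevez, make up the whole intervention arm. Randomising patients was ruled out because they share pharmacies and FHUs.

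**Expected clusters (6.1, Table 3).** About 9 intervention pharmacies are invited with about 80% uptake, and about 60 control pharmacies with about 20% uptake. Table 3 lists 2 intervention FHUs and 17 control FHUs.

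**Sample size (6.11).** "Assuming an alpha of 5%, 90% power and an allocation ratio of 1:1, we estimate that the minimum total sample size to detect differences" comes to 178 patients, or 89 per group. The G*Power output is headed "Proportions: Inequality, two independent groups (Fisher's exact test"), two-sided. The inputs are a control rate of 10% and a difference of 20 percentage points: "our study will be conducted to detect a minimal 20% increase in the rate of discontinuation". The only inflation is for 20% loss to follow-up, giving 111 per group.

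**Primary analysis (6.15.2).** The outcome is "calculated using a GLM model for binary outcome with an identity link function to estimate the risk difference", adjusted for baseline covariates. No pharmacy or FHU term, mixed model, GEE or cluster-robust variance is named. Section 1 repeats both the sample size and the model.

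**Identifiers (Table 5).** Pharmacy code and FHU name are collected but given no role in the analysis.

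**The concern.** Within an intervention pharmacy the same staff recruit, screen and educate the patients. A limited number of GPs (7 and 10 in Table 3) then decide on withdrawal. The protocol itself treats local environment and GP habits as influences on outcome: they are its reason for avoiding patient-level allocation (section 5) and a named confounding domain (section 7). Outcomes within a site should therefore be expected to correlate.

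If they do, 89 patients per arm carry less information than 89 independent patients. Power for the primary comparison falls below the stated figure. A model-based standard error is also too small, so the 5% test rejects too often and the 95% interval covers too rarely. The same effect estimate feeds the NNT (6.15.2) and the cost-effectiveness ratio (6.17.5).

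**Working it through.** **1. Reproduce the plan's figure.** Exact two-sided Fisher test, 0.10 against 0.30, alpha 0.05, by full enumeration:
- 89 per arm: 0.9017, matching the stated 0.9017447.
- 88 per arm: 0.8977.

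So 89 is the minimum, and it holds at an ICC of zero. After attrition, 111 × 0.8 = 88.8, which leaves nothing over.

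**2. Inputs for the clustered calculation.**
- Pharmacies (6.1): 0.80 × 9 = 7.2, about 7 intervention; 0.20 × 60 = 12 control.
- Analysed patients per pharmacy: 89/7 = 12.7 and 89/12 = 7.4.
- Degrees of freedom: 7 + 12 − 2 = 17, critical t = 2.110.
- ICC: not in the protocol. Assumed range 0.01 to 0.10.

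**3. Power with pharmacy as the cluster.**
- Design effect per arm: DE = 1 + (m − 1) × ICC.
- SE of the risk difference: √[(0.30 × 0.70 × DE_int + 0.10 × 0.90 × DE_con)/89].
- Power: probability that a noncentral t on 17 df, with noncentrality 0.20/SE, exceeds 2.110.

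| ICC | DE int | DE con | SE | 0.20/SE | Power |
|---|---|---|---|---|---|
| 0 | 1.00 | 1.00 | 0.0581 | 3.44 | 90% |
| 0.01 | 1.12 | 1.06 | 0.0609 | 3.28 | 87% |
| 0.02 | 1.23 | 1.13 | 0.0637 | 3.14 | 84% |
| 0.05 | 1.59 | 1.32 | 0.0713 | 2.81 | 75% |
| 0.10 | 2.17 | 1.64 | 0.0824 | 2.43 | 63% |

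A normal approximation with the t critical value and a pooled null variance gives 87% / 84% / 75% / 62% for the four positive ICCs, so the choice of formula matters little.

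**4. Type I error of the unclustered 5% test.** With a common rate in both arms it is 2 × [1 − Φ(1.96 × √(2/(DE_int + DE_con)))].
- ICC 0.01 / 0.02 / 0.05 / 0.10: 6.1% / 7.1% / 10.4% / 15.6%.
- Beta-binomial simulation (40,000 runs, both rates 0.10): 6.4% / 7.4% / 10.8% / 16.0%. The same simulation gives 5.4% at ICC 0.

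**5. Width of the unclustered interval.** At 30% against 10%, the correct standard error exceeds the independent one by √[(0.21 × DE_int + 0.09 × DE_con)/0.30] = 1.05 / 1.10 / 1.23 / 1.42 at the same four ICCs.

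**6. FHU as the cluster.** Two intervention FHUs give 89/2 = 44.5 patients each; 17 control FHUs give 89/17 = 5.2 each. Using all 17 is the mild case, because fewer would raise the control design effect.
- Intervention design effect at ICC 0.01 / 0.02 / 0.05: 1.44 / 1.87 / 3.18.
- Type I error of the unclustered test by the formula in step 4: about 8% / 11% / 19%.
- Normal-approximation power: 85% / 78% / 61%, against 92% at ICC 0 on the same formula.
- Effective intervention-arm size at ICC 0.05: 89/3.18 = 28. Recruiting more patients in the same two FHUs cannot raise it beyond about 2/ICC = 40.

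**The case against.** **The SAP may deal with it.** A SAP is promised (6.15) and is not at hand. Section 6.15.2 fixes the link, the effect measure and the covariate adjustment, but not the variance estimator, and an identity-link GLM can carry cluster-robust variance without contradicting it. A reader might infer that the trial's intervals will be too narrow. The protocol does not establish that; it holds for a model-based interval from the GLM as written. The defence does not reach the sample size, which is complete in 6.11 and cannot be restored by an analysis choice.

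**The ICC is unknown and may be small.** This is right. A reader might infer that 90% power is certainly not delivered. At ICC 0 the stated power stands, and at pharmacy ICC 0.01 the loss is about 3 points. Covariate adjustment, and the choice of control FHUs by type and PPI volume (6.1), may lower residual between-site variation. The cluster counts are expected uptake, not commitments. The direction is firm; the figures are conditional.

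**Fisher's test is conservative.** A normal-theory test on 89 independent patients per arm has about 92% power, so a GLM has slightly more room than Fisher. At pharmacy ICC 0.01 the same formula gives 89.8%, so that room is soon used up.

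**The limitation is already stated.** In part: section 7 says that the intervention FHUs were chosen for willingness and that results may not generalise. It does not say that FHU variation cannot be separated from the treatment effect.

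**Tempting repairs that do not work.** Applying Fisher power to a reduced effective sample gives about 79% at pharmacy ICC 0.05, but that power does not belong to a clustered analysis on 17 df, which has about 75%. Clustering on pharmacy also does not capture correlation between pharmacies that share an FHU. The rounding to 111 per group is within the tolerance of a planning guess and is not a fault worth raising.

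**Conclusion.** The point holds, in conditional form. The 90% power in 6.11 is correct arithmetic for independent patients, but section 5 allocates whole sites and the sample size has almost no reserve. Any appreciable within-site correlation takes power below 90%. Under the GLM as 6.15.2 states it, a model-based interval would then be too narrow and the 5% test too liberal.

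The size rests on an assumed pharmacy ICC of 0.01 to 0.10, on 7 and 12 pharmacies of equal size within arm, and on the protocol's 10% and 30%. Over that range power runs from about 87% down to 63%, and the type I error of an unclustered test from about 6% up to 16%. FHU-level correlation does more damage at the same ICC, and with two intervention FHUs it cannot be estimated apart from the treatment effect. The protocol does not support a single figure for the shortfall.

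**What to change.** **6.15.2.** Keep the identity-link GLM for the risk difference. Specify GEE or cluster-robust variance by pharmacy, with a small-sample correction and a t reference (17 df at the expected counts). Apply the same principle to the secondary models and to the cost and QALY models in 6.17. The pharmacy and FHU identifiers are already collected.

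**6.11.** Restate the power as conditional on a declared ICC range and compute it for that analysis, for example about 75% at pharmacy ICC 0.05. Bring the section 1 summary into line. The recruitment target need not change.

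**Section 7.** State that clustering on pharmacy does not remove FHU-level variance, that two intervention FHUs cannot separate this variance from the treatment effect, and that the interval may therefore still be too narrow and the conclusion applies to these FHUs.

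**Cost.** Protocol and SAP wording, wider intervals and a less favourable stated power. No extra patients, sites or data.
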